#### Psychosocial outcomes

Five distinct psychosocial outcomes are measured: (1) Quality of Life via the Patient-Reported Outcomes Measurement Information System (PROMIS) 8-item Ability to Participate in Social Roles and Activities Short Form, designed and validated for use among general populations and individuals with chronic conditions [88, 89]; (2) Depressive Symptoms via the widely used 20-item Center for Epidemiological Studies Depression Scale (CES-D), validated in both general and psychiatric populations [90]; (3) Post-Traumatic Stress Symptoms via an abridged, 8-item version of the Post-Traumatic Checklist for DSM-5 (PCL-5). The full 20-item version has been validated for provisional diagnoses in military and non-military populations [91]. (4) Social Functioning via the 12-item World Health Organization Disability Assessment Schedule (WHODAS) 2.0, designed to be used across all diseases and populations and previously validated in multi-country clinical trials [92]; and (5) Social Support via a 6-item measure of perceived availability of social support that asks participants their confidence that, if needed, adequate support would be available to them across six different domains [93].

#### Treatment adherence

Antenatal adherence is measured by tracking the number of antenatal visits to the clinic, both objectively using the “maternal clinic card” that is filled out by doctors and that mothers carry, and subjectively from participant self-report. ART adherence is measured using the AIDS Clinical Trial Group (ACTG) Adherence Follow-Up Questionnaire, which asks participants details about their HIV medication use patterns over the last 4 days and any reasons for non-adherence [94].

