**Fig. 1 Fig1:**
[figure not shown]
Model for stigma’s effect on treatment adherence

Growing evidence also suggests outcomes in HIV-exposed infants are poorer than unexposed infants [26–29]. The reasons for this are multifactorial and may include poorer birth outcomes (e.g., higher risk of preterm delivery, lower birth weight) [30, 31]. Decreasing stigma and increasing adherence to ART and antenatal care among pregnant mothers diagnosed with HIV, in addition to blocking mother-to-child transmission (MTCT), could improve birth outcomes for the infants (Fig. 1). We consider ART adherence and antenatal effects jointly because their provision is often linked in Botswana. Despite equivocal effects of ART adherence on birthweight [32], reducing stigma to improve mothers’ antenatal adherence to the WHO standard (≥ 4 antenatal visits, with the 1st visit in the 1st trimester [33–36]) could improve infants’ birth outcomes [36, 37]. Achieving stigma reduction at this crucial period is vital for future evaluation of longer-term infant outcomes when stigma may have greater adverse impacts (e.g., breastfeeding and MTCT). We hypothesize that by delivering “Mothers Moving towards Empowerment” (MME) during pregnancy, stigma reduction will persist postpartum and could help sustain ART adherence during a time period in which mothers remain especially vulnerable to stigma.

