### Eligibility

All pregnant women registering to receive antenatal care at these health clinics who are identified as having HIV and meet the inclusion criteria are eligible to be included in the trial; both primiparous and multiparous women may participate. In addition to being a pregnant woman receiving antenatal care and having HIV, participants are screened at the time of recruitment to ensure they meet the study inclusion criteria of being (a) 18–45 years of age, (b) a Botswana citizen, (c) English or Setswana speaking, and (d) no more than 28 weeks pregnant at the time of recruitment (to allow sufficient time to participate in the intervention prior to delivery). Women are expected to be in HIV care per national HIV treatment guidelines [16]; however, they are not required to be on ART treatment at the time of enrollment. The study excludes from participation (1) women who experienced a miscarriage prior to 28 weeks and (2) women unavailable to attend weekly 90-min sessions for eight sessions prior to week 36.

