**Treatment adherence**				
Antenatal adherence	ALL	MME	ALL	1,2,3,4,5
ART adherence (ACTG questionnaire)	ALL	MME	ALL	1,2,3,4,5

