**Covariates**				
Demographic measures	ALL	MME	ALL	N/A
Alcohol use (AUDIT)	ALL	MME	ALL	N/A
Sexual behavior (5 items)	ALL	MME	ALL	N/A
Intimate partner violence (WAST)	ALL	MME	ALL	N/A
**Qualitative** (open-ended; differs at each time points)	MME	MME	MME	N/A
**HIV metrics:** CD4 count and viral load (IDCC records/electronic medical record system)			ALL	1
**Birth outcomes:** birth weight, gestational age, APGAR scores (Delivery Summary Sheet)			ALL	1
**Infant health:** infant mortality, infant HIV status, feeding method, vaccinations, hospitalizations (dates, diagnosis) (“Under 5 Card”: asked from mother at 4 month follow-up)			ALL	1

1 Bivariate comparison of mean (median) scores at 16-week follow-up between intervention and control group

2 Bivariate comparison of change in mean (median) scores from baseline to 16-week follow-up between intervention and control groups

3 Bivariate comparison of mean (median) scores at baseline and post-MME within intervention group

4 Bivariate comparison of mean (median) scores at baseline and 16-week follow-up within intervention group

5 Bivariate comparison of mean (median) scores at post-MME and 16-week follow-up within intervention group

*ALL* all participants

*MME* only intervention participants

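### Antenatal visit counts cannot fall, so the within-MME before/after comparisons show a rise whatever MME does; the between-arm change is sound only if the arms enter at similar gestation

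*Protocol article*

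**What the plan says.** Under Primary outcomes, the Treatment adherence subsection says "Antenatal adherence is measured by tracking the number of antenatal visits to the clinic", taken from the mother's clinic card and from self-report. It gives no counting window, rate or denominator. Statistical analysis says that objective measures take priority over self-report for the antenatal and ART outcomes, so the card count leads.

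The Table 1 row reads "Antenatal adherence ALL MME ALL 1,2,3,4,5". The outcome is thus recorded at baseline, post-MME (MME arm only) and 16 weeks postpartum, and receives all five comparison metrics:

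- Metric 1: "Bivariate comparison of mean (median) scores at 16-week follow-up between intervention and control group".
- Metric 2: "Bivariate comparison of change in mean (median) scores from baseline to 16-week follow-up between intervention and control groups".
- Metrics 3 and 5: within-MME comparisons of baseline with post-MME, and of post-MME with follow-up.
- Metric 4: "Bivariate comparison of mean (median) scores at baseline and 16-week follow-up within intervention group".

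Statistical analysis applies the Wilcoxon signed-rank test to the primary outcomes before and after the intervention in the MME arm, labels this exploratory, and uses the rank-sum test between arms at a 0.05 level. Eligibility admits women "no more than 28 weeks pregnant at the time of recruitment". Condition assignment and blinding states that allocation is not randomised and follows the timing of recruitment.

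**The concern.** A stigma or depression score can move either way, so a before/after comparison at least asks a question that could be answered no. A running visit count cannot. Any woman who attends even once more after baseline adds a positive difference, and no woman can add a negative one. The test then detects that pregnancy went on and care continued, not that MME improved attendance.

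Statistical analysis also makes it a focus to see whether changes from baseline to post-intervention predict later changes. For this outcome the early change largely reflects elapsed weeks. The pilot is meant to support an application for a larger trial, so an automatic p<0.05 on a named primary outcome could be read as a signal.

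The between-arm change raises a separate, conditional issue. A woman who enters earlier has more pregnancy left in which to attend. If the arms differ in gestation at entry, that difference carries straight into metric 2.

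**Working it through.** The plan states no figure for this outcome, so there is none to reproduce.

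**1. Within-arm tests (metrics 3 to 5).** Let k be the number of MME women with at least one further visit. Zero differences drop out and the remaining k are all positive, so the exact two-sided signed-rank p is 2/2^k.

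- k=5: 2/32 = 0.0625
- k=6: 2/64 = 0.031
- k=10: 2/1024 = 0.002
- k=15 (the example MME arm in Sample size and power): 2/32768 = 0.00006

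Six women with one more visit each are enough, even if no one else attends again.

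**2. How often that happens with no MME effect.** This needs assumptions that the document does not give: Poisson visits at 0.15 to 0.35 per week in both arms, entry at 14 to 28 weeks, post-MME eight weeks after baseline, delivery at about 38.5 weeks, and arms of 15/5, 30/10 and 60/20. At the lowest rate, a woman has a further visit within eight weeks with probability 1 − exp(−0.15×8) = 1 − 0.30 = 0.70. That is about 10.5 of 15 women, well above six. In simulation, metric 3 rejected in 99.7 to 100% of trials and metric 4 in 100%. Metric 5 is zero or positive for every woman, depending on visits between post-MME and delivery.

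**3. Does a per-interval count help?** No, because the intervals are not comparable. The baseline interval covers pregnancy up to entry, which varies. The interval to post-MME depends on whether the eight sessions run weekly (about 8 weeks) or twice weekly (8/2 = about 4 weeks). The last interval includes 16 postpartum weeks with no antenatal care.

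**4. Between-arm comparisons under the same null.** The expected spurious difference in metric 2 is the visit rate times the difference in entry gestation; for 4 weeks, 0.15×4 = 0.6 to 0.35×4 = 1.4 visits.

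| MME enters earlier by | Spurious mean difference, metric 2 (visits) | Metric 2 rejects |
|---|---|---|
| 0 weeks | about 0 | 3.4–5.2% |
| 2 weeks | 0.3–0.7 | 5–14% |
| 4 weeks | 0.6–1.4 | 7–42% |
| 6 weeks | 0.9–2.1 | 11–72% |

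Ranges run over visit rates and arm sizes. If MME women enter later, the sign reverses and a real effect could be hidden. Metric 1, the total count at follow-up, rejected in about 3 to 6% for 0 to 4 weeks and in at most 10% at 6 weeks.

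**The case against.** Several objections have force.

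- **The pre/post analysis is labelled exploratory.** This is correct. The main comparison is between arms by intent to treat, and power rests on the rank-sum test. A reader might infer that the primary analysis itself yields a false benefit; the document does not support that. The p-values above concern the exploratory within-arm test only.
- **Cumulative counting is inferred.** This is also correct, since no window is stated, and self-reported counts could fall between interviews. But the card count has priority, and the per-interval alternative fails too.
- **Control counts rise as well.** A reader might infer that metric 2 must show improvement with no MME effect. It does not: with equal entry gestation the rise cancels and rejection stays near 5%. The document shows no imbalance and gives no direction, and timing of recruitment is not said to mean gestational age.
- **Baseline differences will be adjusted for.** The Discussion says so in general terms, and exploratory regression on study arm is planned. Against this, the Covariates section reserves its variables for description and does not list gestation at enrolment, and the named between-arm tests are unadjusted.

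Two further readings should be set aside. Metric 1 includes visits made before enrolment, which dilutes an effect rather than creating one. The standard with four or more "antenatal visits, with the 1st visit in the 1st trimester" appears in the Introduction as background; first-trimester attendance is not an outcome of this trial.

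**Conclusion.** The within-MME before/after comparisons for "Antenatal adherence" are uninformative. On the running-count reading, metrics 3 and 4 are all but certain to be significant in an arm of 15 or more at the assumed visit rates, and metric 5 can only be zero or positive. The formula 2/2^k needs no assumption about visit rates; the 99.7 to 100% rejection figures do.

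Metric 2 is valid when entry gestation is similar and vulnerable when it is not. Nothing in the non-random assignment protects that balance, but an imbalance is a possibility and not something the document shows. The bias could go either way, and its size follows from assumed rates. Metric 1 is diluted but not materially biased unless the imbalance is large.

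The problem is confined to one row of Table 1 and to exploratory tests. It is still a stated analysis that would give a wrong message, and correcting it is nearly free.

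**What to change.** 1. In Table 1, delete metrics 3, 4 and 5 for antenatal adherence. State that its change from baseline to post-MME will not be used as evidence of benefit.
2. State the counting window. Define the between-arm endpoint as visits after enrolment up to delivery, from the maternal clinic card. On the running count this is metric 2, because no antenatal visits follow delivery.
3. Adjust that comparison for gestational age at enrolment, which eligibility screening already establishes; the planned regression on study arm can carry it. Do not scale by weeks from enrolment to delivery: that quantity arises after assignment, and timing of delivery is itself an outcome.
4. Keep total visits at follow-up (metric 1) as a supporting comparison.

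The change takes one table row and a sentence or two, with no new data collection. The cost is one exploratory pre/post result for this outcome, and one covariate added in a small sample.

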#### HIV metrics

The two most common biological measures of HIV are CD4 count and viral load, which are both extracted from the IDCC electronic medical record system along with the date(s) of each test and the date of ART initiation. Due to limited resources, we are not able to measure these metrics directly and therefore rely on clinical measurement and documentation (noting that documentation for viral load may be sparse due to inconsistent following of recommendations of a viral load test in the 3rd trimester). When data are available, the dates may not align with any of our time points. Due to these pragmatic concerns, we opt to collect these metrics only once at the end of the study and then ascertain how best to proceed for analysis.

### Secondary outcomes

Because increasing adherence to antenatal care and to ART is hypothesized to improve birth outcomes such as low birthweight and preterm delivery [31] (Fig. 1) and early infant health such as survival and HIV status, we examine these in exploratory analyses (study not powered for these outcomes).

#### Birth outcomes

All birth outcomes will be extracted from the Delivery Summary Sheet, including the infant’s date of birth, birth weight (grams), gestational age (number of weeks), date of discharge (or death, if child died before discharge), and APGAR scores at 1, 5, and 10 min [95].

#### Infant health

All infant health metrics are extracted from the “Under 5 Card,” which is carried by the mother and filled out by a doctor to track infant’s developmental outcomes. We chose the 16-week time point for follow-up because that is the first time that all measures are recorded on this card. This includes infant mortality (< 16 weeks), infant HIV status (i.e., if mother-to-child transmission occurred), feeding method (breastfeeding, formula, both), vaccination schedule, and hospitalization for any illnesses (up to three diagnoses and admission/discharge dates).

### Covariates

Additional measures include sociodemographic information (date of birth and age; racial, ethnic, and/or tribal background; sex at birth and gender identity; sexual orientation; relationship status; highest education level; estimated total family income; employment pattern; money for basic necessities; assistance from government or local community leadership; membership in private medical aid; homelessness; and housing status, including household items). Three additional scales are included: (1) alcohol use via the 10-item Alcohol Use Disorder Identification Test (AUDIT) [96, 97]; (2) sexual behavior via five questions about number of sex partners in the past month; how often used condoms during sex with regular partner(s) in past month; how often used condoms with casual partners in past month; how often used condoms for paid sex in past month; and how often anal sex in past month; and (3) intimate partner violence via the 8-item Woman Abuse Screening Tool (WAST) [98]. These covariates will be collected at baseline and will be used in a purely descriptive fashion to characterize the sample.

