In addition, we incorporated a section on general strategies for HIV status disclosure, emphasizing empowerment skills [85] when a mother wishes to disclose her HIV status. Should disclosure to a partner lead to domestic violence, the MME intervention provides all participants with contact details for a women’s shelter that provides services to women who have experienced domestic violence, as well as for psychological services at Princess Marina Hospital’s Psychiatric Clinic and the University of Botswana’s Psychology Clinic. Both intervention and control participants who disclose abuse to study personnel are referred for counseling via our expert in-country psychiatrist consultant (PO), or a qualified mental health practitioner he designates, for further counseling and linkage to available support services.

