### Intervention procedure

The 8 sessions of the intervention occur weekly for about 90 min per session. Each session focuses on a particular theme including Introduction and Defining Stigma, Common Myths and Facts about HIV Transmission, Common Myths and Facts about Prevention of Mother-To-Child Transmission (PMTCT), The Road to Self-Acceptance and Freedom: Coping Strategies, Coping with Discrimination: Social Support and Self-Disclosure, The Road to Self-Acceptance and Freedom Part 2: Automatic Thoughts, What Matters Most, Review, and Graduation. Homework is assigned at each session and reviewed the next session. Certificates are issued to participants who complete the intervention (≥ 5 sessions) in a graduation ceremony. In consultation with local experts, we developed a concluding ceremony intended to convey “WMM” (i.e. “good mother” status) via the bestowing of ceremonial shawls that are typically provided when women become married and are ready to bear children. Finally, participants can leave this study at any time and, if choosing to withdraw, may decide to inform the study staff as to why, but are not required to do so.

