In regard to adverse events, we anticipate two events that may occur, intimate partner violence, and depression and suicidal ideation. In order to protect the privacy of participants and to mitigate the possibility of intimate partner violence, protections for participant privacy will include the following: contact only with the participant; no study-related information will be left on answering machines or other devices; no study-related information will be left with individuals who reside within the household. These procedures will also be followed when participants are contacted about the longitudinal evaluation at 16-week follow-up. When an instance of intimate partner violence is disclosed either during an anti-stigma group session or during the baseline or follow-up evaluation, the study team member who identified the event will report the date, description of the event, duration, severity, measures used to ameliorate effects of the event, and type of referral. The Project Director (AHO) will be notified immediately, and the report form will be reviewed and signed by the PIs (LHY and MB) within 24 h who will be responsible for ensuring that appropriate actions have been taken. The participant will be immediately referred to psychiatric counseling by a clinician under the supervision of our expert in-country psychiatrist Consultant (PO) and other supportive services (e.g., domestic violence support group). The clinician will conduct an in-person clinical evaluation within 24 h, and if the participant is found to be experiencing significant psychiatric distress, this clinician will immediately connect the participant with clinical services in the Princess Marina Hospital Department of Psychiatry, which will address any distress via in-person outpatient meetings and continuing therapy sessions as needed.

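### Partner violence is an anticipated adverse event, but the protocol contradicts itself on whether WAST is taken after baseline and excludes it from any comparison between arms

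*Protocol article*

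**What the plan says.** The Data management section states of adverse events that "we anticipate two events that may occur, intimate partner violence, and depression and suicidal ideation". Intervention rationale and components describes teaching on disclosure of HIV status and plans for the case that begins "Should disclosure to a partner lead to domestic violence".

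Two places govern the WAST, and they differ:

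- Table 1 lists it under covariates for all participants at baseline, for MME participants only after the intervention, and for all participants at 16 weeks. The comparison metric is N/A.
- The text under Covariates, which includes WAST among the additional scales, says: "These covariates will be collected at baseline and will be used in a purely descriptive fashion to characterize the sample".

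The Table 1 outcomes measured on the same schedule carry metrics 1 to 5. Metric 1 compares the arms at 16 weeks. Metric 2 is: "Bivariate comparison of change in mean (median) scores from baseline to 16-week follow-up between intervention and control groups".

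The Data management section starts the partner-violence report when an instance is "disclosed either during an anti-stigma group session or during the baseline or follow-up evaluation". The DSMB reviews adverse events and safety outcomes every six months. Publications are to give a short account of events and of how they were handled.

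**The concern.** The protocol recognises a plausible path from the intervention to harm and has a scale for that harm, yet it excludes the scale from the between-arm analysis. This is more than detail left to a statistical analysis plan. An analysis plan that compared 16-week WAST by arm would have to depart from both the N/A entry and the descriptive-only sentence.

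The protocol treats its other anticipated event differently. Depression has the CES-D, which is an outcome with metrics 1 to 5 and also a named, score-based detection route at baseline and 16 weeks. For partner violence, the adverse-event text names disclosure only.

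At stake is the safety information carried into the planned multisite trial. Without a post-baseline WAST compared by arm, what remains is a set of disclosed events, and the two arms have very different opportunities to disclose.

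**Working it through.** **1. The two schedules side by side**

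| | Baseline | Post-intervention | 16 weeks | Use |
|---|---|---|---|---|
| Table 1 | all | MME only | all | no comparison (N/A) |
| Covariates text | yes | not mentioned | not mentioned | descriptive only |

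If the Covariates text is followed, no WAST is taken after baseline. If Table 1 is followed, the 16-week data exist in both arms but are not compared. The Statistical analysis section does not fill the gap. It lists between-arm tests of baseline characteristics, maternal primary outcomes and infant outcomes, with no test of post-baseline partner violence.

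**2. Post-baseline occasions on which violence can be disclosed**

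The baseline visit is left out, because under Recruitment it comes before allocation is disclosed and so cannot detect violence caused by MME.

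- MME: 8 sessions (Intervention procedure) + 1 follow-up evaluation = 9. The MME-only post-intervention assessment would make 10.
- TAU: 1 follow-up evaluation. The Comparator section excludes these women from the post-intervention assessment.

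**3. Illustration of the possible bias**

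The documents give no disclosure probability, so q is assumed. With equal true violence in both arms and an independent probability q of disclosure at each of k occasions, P(detected) = 1 − (1 − q)^k.

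| q (assumed) | MME, k = 9 | MME, k = 6 (5 sessions + follow-up) | TAU, k = 1 | Ratio, 9 v 1 | Ratio, 6 v 1 |
|---|---|---|---|---|---|
| 0.05 | 37% | 27% | 5% | 7.4 | 5.3 |
| 0.10 | 61% | 47% | 10% | 6.1 | 4.7 |
| 0.20 | 87% | 74% | 20% | 4.3 | 3.7 |
| 0.50 | about 100% | 98% | 50% | 2.0 | 2.0 |

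A common q is a strong assumption. Suppose the follow-up visit elicits disclosure with probability 0.50 and each session with 0.05. Then MME detection is 1 − 0.95^8 × 0.50 = 1 − 0.663 × 0.50 = 67%, against 50% in TAU, a ratio of 1.3. The direction holds whenever sessions yield any disclosure not otherwise obtained. The size is not determined by the documents.

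**4. What a 16-week WAST comparison could deliver**

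Assume 40 women at 3:1, that is 10 TAU and 30 MME. The protocol uses 40 as an example size for a correlation, so this is an assumption about the arms. At two-sided 0.05, simulated Mann-Whitney power is about 0.27, 0.54 and 0.75 for shifts of 0.5, 0.8 and 1.0 SD. Fisher's exact test has power of about 0.15 for 10% v 30% screening positive.

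**The case against.** Four points can be made for the plan.

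- **No by-arm comparison of events is stated.** A reader might infer that harm will be judged on adverse-event counts by arm. The documents do not say so. They promise a brief account of events, and the DSMB also sees safety outcomes, which are not defined. A Data Safety and Monitoring Plan is cited but not shown and may specify more. This stands: the ascertainment problem is a warning about how event reports could be read. It does not remove the N/A entry, the descriptive-only sentence or the conflict over timing.
- **The contact count is easily overstated.** A reader might count every contact and arrive at 11 v 2. That includes the baseline visit, which cannot detect harm from MME. The relevant count is up to 9 or 10 v 1, and fewer in MME for women who miss sessions.
- **The arms are not measured identically on WAST.** Table 1 adds a post-intervention administration in MME only. Only baseline and 16 weeks match, so only these can support a comparison between arms.
- **The comparison would not settle the question.** A reader might infer that adding it would show whether MME raises or lowers partner violence. It would not: allocation follows recruitment timing and overflow, the control arm is small, and power is low. This limits what can be claimed, but it also applies to the outcomes that the protocol does compare, so it is no reason to omit this one.

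**Conclusion.** The point holds as a conflict within the protocol and an explicit exclusion. The Covariates text and Table 1 cannot both be followed on WAST timing, and under either one an anticipated harm has no post-baseline comparison between arms. This rests on the wording alone.

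The ascertainment argument is secondary. The post-baseline imbalance of up to 9 (or 10) occasions v 1 follows from the documents. The resulting detection ratio does not: it runs from about 7.4 to 2.0 under a common assumed q of 0.05 to 0.50 with all sessions attended, and falls to about 1.3 when the shared visit is assumed much more productive than a session. The documents do not support the statement that harm will be judged on event counts. Nor would the amended analysis be evidence that MME is safe or unsafe. It would give an imprecise, non-randomised estimate from the time points at which both arms are measured alike, which is better than none. The change should be made.

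**What to change.** 1. Reconcile the Covariates text with Table 1 so that WAST is kept at 16 weeks in both arms, and exempt it from the descriptive-only sentence.
2. In Table 1, change the WAST comparison metric from N/A to 1 and 2. Label it a pre-specified safety measure, report the between-arm estimate with a confidence interval, and supply it to the DSMB.
3. Report partner-violence events by arm and by route of detection (group session, MME-only post-intervention assessment, assessment common to both arms), with the number of women in each arm.
4. State that the WAST estimate is imprecise and non-randomised and is not proof of safety, and that event reports by arm reflect unequal opportunity to disclose.

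If Table 1 is what the sites follow, the cost is wording and one further row of analysis. If the Covariates text is being followed, an 8-item scale must be added to an existing visit. Recruitment began in March 2019, so 16-week data could not be recovered for women already past that visit.
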